### Children and adolescent data collection

Youth and parent measures will be collected by study staff via telephone at the beginning of treatment, and at three and six months into treatment (approximating end of treatment; post-treatment data for some and ‘still in treatment’ for others).

### Phase I study

Phase I will involve describing current supervision practices and establishing a baseline for current practice, specifically identifying extent of use of gold standard strategies and examining any association with clinician fidelity and client outcomes.

### Procedure

Clinicians and supervisors will complete self-report study measures via a web-based survey at the beginning and the end of Phase I. At the beginning of Phase I, clinicians and supervisors will participate in a two-day study procedures and TF-CBT booster training. Study training will focus on youth recruitment and mobile tablet device training (e.g., session audio recording, uploading, and data collection from supervisors/clinicians). Supervision meetings with study clinicians will be audio recorded using tablet devices and electronically submitted to our research team using a secure Health Insurance Portability and Accountability Act (HIPAA)-compliant server. In Phase I, 15 randomly selected meetings per supervisor will be coded, with selection distributed across participating clinicians (approximately 400 meetings). A random sample of three TF-CBT sessions per clinician, per study client, will be coded for TF-CBT fidelity. All coders will be trained to an established criterion of 80% agreement on training tapes. During the study, a random 20% of all coded sessions (supervision and TF-CBT) will be coded by two coders to test inter-rater reliability. If reliability is less than 80% on two successive reviews, booster training will be conducted.

### Measures

The primary outcomes of interest are supervision practices, clinician fidelity, and client outcomes. We also examine factors that may relate to supervision practices and fidelity, including supervisor and clinician background, training and experience, therapist knowledge of TF-CBT practice, therapist-supervisor relationship, organizational climate, attitudes towards EBTs, and therapist burnout.

### Child symptoms and functioning

To assess child PTS, study staff will administer the UCLA Post Traumatic Stress Disorder Reaction Index (PTSD-RI) [62], using a severity cutoff of 21 and higher or algorithm scoring for likelihood to meet diagnostic criteria. This 20-item measure assesses PTS and demonstrates good convergent validity and good to excellent test-retest reliability, with Cronbach’s α in the range of 0.90 for the total scale [63]. To assess child functioning, the Strengths and Difficulties Questionnaire (SDQ) will be administered, a 25-item measure with scales for Emotional Symptoms, Conduct Problems, Hyperactivity/Inattention, Peer Relationship Problems, and Prosocial Behavior [64]. Parents will complete the SDQ on all children; children 10.5 years and older will complete the self-report version of the SDQ. The SDQ has been found to have good discriminant validity, acceptable levels of test-retest reliability, and a Cronbach’s α of 0.73.

### Therapist/supervisor characteristics

We will use a study-created measure based on the Therapist Background Questionnaire [1] and the PWS to capture demographics, training, past experience, tenure in current organization, role, years in current role, caseload composition and size, other supervision received, and utilization of TF-CBT, among other important background characteristics.

### Supervisor-clinician relationship

Given the potential importance of the supervisor-clinician relationship, we will use three measures to assess this relationship: Leader Member Exchange [65], Supervisor Working Alliance Inventory (SWAI) [66,67], and the Supervision Alliance Scale (SAS) [66,68]. In Phase I, both supervisors and clinicians will report on the Leader-Member Exchange; only clinicians will report on the SWAI and SAS.

### Aim 1: Describe and establish baseline use of supervision strategies, when provided with implementation support

#### Analyses

We will analyze coded supervision sessions and self-report measures using grand means and variability (i.e., over all sessions) and supervisor-level means and variability for frequency and intensity, building on procedures in Garland et al. [30]. The SPQ and PWS will be analyzed with descriptives at baseline and we will explore for significant changes over time. These analyses will establish a baseline for the types of supervision practices used overall and within-supervisor variability. We will use the coded TF-CBT sessions to obtain a baseline for TF-CBT fidelity. We will explore univariate descriptives and change over time for all other measures described above, as well as the relation between client outcomes, clinician fidelity, and supervision content, strategies, and focus.

### Phase II study

In Phase II of the study, all clinicians will be randomized to one of two supervision conditions: Symptom and Fidelity Monitoring (SFM) or SFM plus Behavioral Rehearsal (SFM + BR). We will randomize by clinicians because they are our primary unit of analysis. Supervisors will provide both conditions to balance the impact of individual supervisor/agency factors across conditions. We will monitor supervisor adherence to condition protocol and experimental drift through coding of audiotapes of supervision sessions. During Phase II, four randomly selected meetings per supervisor (two for each condition, distributed across participating clinicians) will be reviewed within a two-week window of the supervision meeting occurring (which is possible due to near real-time uploading with the use of the mobile device system) by research assistants blind to study condition. If experimental drift is identified, supervisors will be contacted within two weeks for a booster training on the supervision conditions. Supervisors will receive a biweekly email on condition adherence so that all supervisors receive regular communication from our team related to provision of supervision conditions.

Phase II has the added benefit of a within-subject design, in which clinicians retained from Phase I serve as their own controls prior to randomization. Given clinician attrition and replacement, some clinicians will not have Phase I data, and therefore will only be part of the between-subject analyses. Fidelity scores will be obtained from the three Phase II enrolled clients per clinician to obtain precise and reliable estimates of effect (see earlier ‘Objective TF-CBT fidelity’ section) and to increase statistical power for detecting differences between the two intervention conditions.

### Description of phase II supervision conditions

#### Symptom and fidelity monitoring (SFM)

Symptom Monitoring involves clinicians monitoring key symptoms each session using brief measures via the tablet device. We use the measures recommended as part of the WA TF-CBT Initiative: the child-completed Screen for Child Anxiety-Related Emotional Disorders (SCARED)—Anxiety and PTS Subscales [73,74] to assess PTS/anxiety and the caregiver-completed externalizing subscale of the Pediatric Symptom Checklist-17 (PSC-17) [75] to assess externalizing behavior. Using a program created for this study, which builds on [name] monitoring system [43], symptoms will be scored and graphed over time to provide a pictorial representation of improvement or deterioration, and reviewed in supervision. For Fidelity Monitoring, clinicians will complete a brief, standard TF-CBT checklist after each session (via tablet) that also will be reviewed in supervision. The supervisor will have a slightly elaborated version that includes follow-up queries for TF-CBT components and key CBT techniques (assigning/reviewing homework, role-play), and a cue to plan for the upcoming session. The goal is to determine if systematic monitoring and review—of symptoms and indirect fidelity—is sufficient to improve fidelity and client outcomes.

### Symptom and fidelity monitoring plus behavioral rehearsal (SFM + BR)

The SFM + BR condition includes the SFM components and an additional, multipurpose strategy—behavioral rehearsal (BR). Given concerns about relying on clinician self-report of fidelity (i.e., indirect methods) and the importance of skill building, the inclusion of BR is a potentially high-yield addition [27]. In SFM + BR, supervisors will conduct a TF-CBT component BR (e.g., five to ten minutes) relevant to an upcoming session in each supervision meeting and provide feedback. Supervisors will have a short set of guidelines (e.g., bulleted form) that detail expected content and techniques for BR of each TF-CBT component. Guidelines focus specifically on common challenges for TF-CBT components (e.g., dealing with avoidance, homework assignment/review).

### Procedure

In the beginning of Phase II, supervisors will participate in a two-day training on the Phase II supervision conditions and study procedures, and specifics on how to systematically integrate gold standard elements into supervision. Training will include didactic information, benefits of SFM and BR, modeling of SFM and SFM + BR use, and coached supervisor practice of SFM and SFM + BR procedures and their use in supervision meetings. Trainers will provide clinician vignettes and pre-loaded SFM data on the tablets for supervisors to use in practicing both experimental conditions. Following recommendations on using BR in training [36], the SFM + BR practice vignettes will also include a supervisor role-play guide for the clinician role, to make the role-plays and coached practice opportunities as helpful as possible. To reinforce their future use, supervisors will be asked to discuss how they think the strategies could enhance their supervision of TF-CBT. Training will also include orientation to the experimental design and trial procedures, with particular emphasis on the importance of condition adherence and preventing experimental drift.

### Supervisor report of TF-CBT fidelity

A modified version of the BPC created by the study team, the Supervisor BPC (S-BPC), will be used to assess supervisor report of clinician fidelity to TF-CBT from supervision meetings.

### Acceptability and feasibility of the phase II conditions

The Supervisor Interview (SI) [76] is a qualitative interview and was used previously by our team to evaluate feasibility and acceptability of an expert consultation model for child welfare workers. The SI has been revised for this study to include questions specific to Phase II SFM and SFM + BR.

### Aim 2: Evaluate effects of supervision condition (SFM vs. SFM + BR) on clinician fidelity and client outcomes (phase II)

#### Analyses

We will use Hierarchical Generalized Linear Models (HGLM) to test Aim 2, with the hypotheses that fidelity and client outcomes will be higher for SFM + BR than SFM and higher for SFM than supervision in Phase I. A two-level HGLM will predict fidelity using individual-mean fidelity scores for each client per clinician as the dependent variable and supervision as the independent variable for client functioning. These analyses are sufficiently powered at 0.8 to detect small effect sizes (0.35) with clinician-level Intraclass Correlations Coefficients (ICCs) less than 0.04 and small to moderate effect sizes (0.4) with ICCs as high as 0.21. To test for client functioning, we will build three-level longitudinal models, with level one variables representing time and child functioning scores, level two representing child-level factors, and level three representing clinician-related factors. These analyses are sufficiently powered at 0.8 to detect small effect sizes with clinician ICCs up to 0.24 and all conceivable moderate or large effects.

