### Clinician and supervisor participants

Participants will include 35 supervisors and 130 clinicians from an estimated 15 to 20 agencies. Agencies were selected from those in the WA TF-CBT Initiative with consideration of statewide geographic representation. Each agency has one to four supervisors and a potential clinician participant pool of 2 to 15 qualifying clinicians based on study inclusion and exclusion criteria. Eligible supervisors were identified during study development with additional supervisors recruited at the beginning of Phase I. Eligible clinicians must be: trained in TF-CBT as part of the WA TF-CBT Initiative and/or have completed the TF-CBT web training with at least one TF-CBT case underway; at least 50% FTE employees at one of the participating agencies; supervised by one of the participating supervisors; and able to provide TF-CBT in English. We propose only two exclusionary criteria: immediate plans to leave the agency or transition into a non-child/adolescent caseload carrying position. Clinicians and supervisors who exit the study will be replaced with new clinicians and/or supervisors who are similarly trained in TF-CBT and study protocols.

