### Children and adolescents

We will recruit one child/family per clinician in Phase I, and three children/families per clinician in Phase II. Eligible children and adolescents will be clients at one of the participating agencies. Inclusion criteria include: age 6–17; trauma history; significant posttraumatic stress (PTS) symptoms; live with a parent/legal guardian who is willing to participate in the study; the child is English-speaking; and treatment approach will be TF-CBT. Exclusionary criteria are intentionally limited and include only: presence of a pervasive developmental disorder or cognitive impairment and parental serious mental illness. Clinicians are asked to introduce the study to caregivers of all potentially eligible youth who meet these inclusion and exclusion criteria. If interested, study staff proceed with recruitment.

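### The SFM + BR versus SFM fidelity model names no baseline covariate, although a pre-randomization fidelity score is already collected; using it would bring a modest gain in precision

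*Protocol article*

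**What the plan says.** In the protocol article, the Analyses paragraph under Aim 2 describes a two-level model for fidelity. The outcome is the mean fidelity score per client within clinician, "as the dependent variable and supervision as the independent variable". No covariate is named there. For client functioning, the same paragraph describes a three-level model with child-level and clinician-related factors, and the Aim 4 analyses control for covariates that are not listed.

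Phase I fidelity comes from three coded sessions of one case per clinician (Phase I, Procedure; Objective TF-CBT fidelity). The Phase II study section refers back to the same fidelity measure. It says that clinicians retained from Phase I act as their own controls, and that "some clinicians will not have Phase I data, and therefore will only be part of the between-subject analyses".

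On recruitment, the section on children and adolescents says: "Clinicians are asked to introduce the study to caregivers of all potentially eligible youth". Child measures are taken by study staff at the start of treatment.

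**The concern.** Clinician fidelity is a primary outcome and the clinician is the randomized unit. A fidelity score from before randomization is the natural baseline for comparing arms, because it removes part of the between-clinician variance. Read together, the Aim 2 and Phase II passages suggest that this score serves the before-after contrast while the arm comparison runs without it. Some precision on a primary outcome would then be given up, and the data to recover it are already in the database.

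A second, separate matter is case mix. Clinicians are randomized, and they then introduce families to the study. They can hardly be unaware of their condition, since one arm rehearses in every supervision meeting. Randomization balances clinicians in expectation. It does not guarantee that the children enrolled afterwards are alike in the two arms, and fidelity is scored case by case.

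**Working it through.** **Inputs from the protocol article.** "Participants will include 35 supervisors and 130 clinicians from an estimated 15 to 20 agencies". "We will recruit one child/family per clinician in Phase I, and three children/families per clinician in Phase II". Power of 0.8 for the fidelity model is claimed in two scenarios (Aim 2, Analyses). One is an effect of 0.35 when the clinician ICC stays below 0.04. The other is given as "small to moderate effect sizes (0.4) with ICCs as high as 0.21".

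**Assumptions, not in the article.** Two-sided alpha 0.05; 65 clinicians per arm; stability ρ of the clinician effect between phases, 0.5 to 1; share q of clinicians with Phase I data, 50% to 100%.

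**1. The plan's own power.** Effective n per arm = 65 × 3 / (1 + 2 × ICC), and power = Φ(d × √(n/2) − 1.96).
- d = 0.35, ICC 0.04: n = 195/1.08 = 180.6, power 0.914.
- d = 0.40, ICC 0.21: n = 195/1.42 = 137.3, power 0.912.

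The stated 0.80 is therefore not reproduced with all 130 clinicians. About 93 to 94 clinicians with three children each give 0.80 in both scenarios (94 clinicians: 0.807 and 0.805). The two statements agree with each other, and 0.8 reads as a floor. I carry both 130 and 94 forward.

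**2. What one Phase I case can explain.** With total variance 1, a clinician's mean over three Phase II cases has variance ICC + (1 − ICC)/3. Its correlation with one Phase I case is r = ρ × ICC / √(ICC + (1 − ICC)/3).
- ICC 0.04, ρ = 1: r = 0.04/√0.360 = 0.067, r² = 0.0044.
- ICC 0.21, ρ = 1: r = 0.21/√0.4733 = 0.305, r² = 0.093.
- ICC 0.21, ρ = 0.5: r = 0.153, r² = 0.0233.

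**3. Variance after adjustment.** Weighting by information, the variance ratio is 1 / [q/(1 − r²) + (1 − q)].
- ICC 0.21, best case (ρ = 1, q = 100%): ratio 0.907, a reduction of 9.3%; 1/0.907 = 1.10, so about 10% more effective clinicians.
- ICC 0.21, weakest case (ρ = 0.5, q = 50%): 1/[0.5/0.9767 + 0.5] = 0.988, a reduction of 1.2%.
- ICC 0.04, over the same range: a reduction of 0.1% to 0.4%.

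**4. Power after adjustment.**

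| Scenario | Clinicians | Before | After |
|---|---|---|---|
| d 0.35, ICC 0.04 | 130 | 0.914 | at most 0.915 |
| d 0.35, ICC 0.04 | 94 | 0.807 | at most 0.809 |
| d 0.40, ICC 0.21 | 130 | 0.912 | 0.915 to 0.936 |
| d 0.40, ICC 0.21 | 94 | 0.805 | 0.809 to 0.841 |

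**5. Case mix.** No arithmetic is possible. The article gives neither a relation between child severity and coded fidelity nor any figure for enrolment by arm.

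**The case against.** The strongest reply is that the article does not say supervision is the only predictor, although a reader might infer it. Naming the independent variable identifies the exposure and is not a covariate list. The sentence is also garbled: it sets out to predict fidelity but reads "as the dependent variable and supervision as the independent variable for client functioning". A condensed article may leave covariates to the full protocol or analysis plan. This stands, so the point concerns what the described model names, not a proven exclusion.

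A joint analysis may even be intended. Aim 2 also hypothesizes that SFM exceeds Phase I supervision, so supervision could be a three-level factor with Phase I and Phase II cases in one model. That is close to the change proposed here. However, the Phase II study section speaks of separate between-subject analyses and never says how Phase I scores enter the arm contrast, so the ambiguity remains.

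A reader might also infer large gains. The formula in step 2 with full stability and complete Phase I data gives r² = 0.169 at ICC 0.30 and 0.375 at ICC 0.50, or 20% and 60% more effective clinicians. The article gives no fidelity ICC above 0.21, so it does not support those figures. Nor does it show a power shortfall that needs repair: both stated scenarios reach about 0.91 with 130 clinicians.

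Finally, a reader might infer that the fidelity contrast is biased by selective enrolment. The article asks clinicians to invite all eligible families, and its Limitations section already concedes that enrolled cases may be unrepresentative. That makes the risk plausible, but differential enrolment by arm is neither shown nor quantified.

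**Conclusion.** The point holds as a modest efficiency and clarity matter. The fidelity model, as described, names supervision and no baseline covariate, while Phase I fidelity is pre-randomization, already collected and coded with the same instrument. At the plan's ICCs, using it lowers the variance by at most 0.4% (ICC 0.04) or by about 1% to 9% (ICC 0.21). Power rises by at most about 4 points, if only about 94 clinicians contribute, and by about 2 points with 130.

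These sizes rest on assumed stability, retention, alpha and allocation, and on Phase I supplying one case per clinician, which makes it a noisy baseline. The unadjusted comparison of randomized clinicians is a legitimate analysis. The case-mix risk justifies a table and a sensitivity analysis; it does not justify a claim of bias.

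**What to change.** Before arms are compared, state that the SFM + BR versus SFM fidelity comparison uses the clinician's Phase I fidelity as a baseline.

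- **Preferred:** one model for Phase I and Phase II case fidelity, with a common mean for both arms before randomization and arm-specific means in Phase II. The covariance between phases should be estimated freely, since a single clinician intercept would force full stability.
- **Alternative:** Phase I fidelity as a covariate with a missing indicator. Whether a clinician has a Phase I score is settled before that clinician is randomized.

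Either way, every randomized clinician stays in. Rewrite the garbled model sentence at the same time.

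Also tabulate child baseline PTSD-RI, parent SDQ and age by arm, and report a sensitivity analysis of fidelity adjusted for them. This addresses measured imbalance only.

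The cost is a few lines of specification and one extra table. No new data are needed.

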**Methods/Design:**

The study has two phases. We will conduct an initial descriptive study (Phase I) of supervision practices within public mental health in Washington State followed by a randomized controlled trial of gold standard supervision strategies (Phase II), with randomization at the clinician level (i.e., supervisors provide both conditions). Study participants will be 35 supervisors and 130 clinicians in community mental health centers. We will enroll one child per clinician in Phase I (N = 130) and three children per clinician in Phase II (N = 390). We use a multi-level mixed within- and between-subjects longitudinal design. Audio recordings of supervision and therapy sessions will be collected and coded throughout both phases. Child outcome data will be collected at the beginning of treatment and at three and six months into treatment.

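### The Aim 2 client-outcome model names no adjustment for the beginning-of-treatment score; if the baseline difference between conditions is left free, the condition test gives up about 15-35% in variance

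*Protocol article*

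**What the plan says.** Under Aim 2, Analyses, the article describes the client-outcome model in one sentence: "we will build three-level longitudinal models, with level one variables representing time and child functioning scores". Child-level factors are placed at level two and clinician-related factors at level three. Neither set is listed.

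The section on child and adolescent data collection gives the only measurement times: "at the beginning of treatment, and at three and six months into treatment". In Phase II, "all clinicians will be randomized to one of two supervision conditions", so condition is a clinician-level factor. The planned numbers are 130 clinicians and "three children per clinician in Phase II (N = 390").

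The power statement for this model reads "These analyses are sufficiently powered at 0.8 to detect small effect sizes with clinician ICCs up to 0.24". The sentence gives no number for a small effect. It does not say whether the effect is standardized on a single visit, on change or on a slope, and it gives no correlation between visits. The preceding sentences, on the fidelity model, do give numbers, for example "small effect sizes (0.35) with clinician-level Intraclass Correlations Coefficients (ICCs) less than 0.04".

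**The concern.** A model with time at level one and only three score times most naturally takes the beginning-of-treatment score as an outcome. What matters then is how the model treats the difference between conditions at that first visit. If it is estimated freely, the effect of condition is read from the condition-by-time term, which subtracts a noisy baseline in full instead of weighting it by how well it predicts the outcome.

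Two things are at stake in the randomized comparison of SFM + BR with SFM:

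- **Precision.** The comparison is less precise than the collected data allow.
- **Chance imbalance.** A change contrast over-corrects for a chance baseline difference. The condition whose children happen to start worse tends to show more improvement through regression to the mean. With 65 clinicians per condition (assuming equal allocation), some imbalance is to be expected.

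The point concerns the client-outcome model only, not the fidelity model.

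**Working it through.** **Inputs from the article.** 130 clinicians, 3 children each, 390 children; visits at 0, 3 and 6 months; power 0.8; clinician ICC up to 0.24.

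**Assumptions, because the article does not state them.** Equal allocation (65 clinicians and 195 children per condition); two-sided 5%; no loss; effect d = 0.35 in single-visit SD units, borrowed from the fidelity sentence; equal variance and equal correlation rho between visits; the ICC of 0.24 applying to every contrast unless stated otherwise.

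**1. The plan's own figure.** The design effect is 1 + 2(0.24) = 1.48. With one score per child, SE = sqrt(2 x 1.48/195) = 0.123, and power = Phi(0.35/0.123 - 1.96) = 0.81. The stated 0.8 is matched, but this does not identify how it was obtained (see the objection).

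**2. What the linear-time test estimates.** With three equally spaced visits, the slope weights are -1, 0 and +1. The condition-by-linear-time contrast is thus 6 months minus baseline, and the 3-month score gets no weight. An exact generalized least squares calculation gave the same power for linear and for categorical time when the baseline means are free.

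**3. Variance factors, relative to one score per child.**
- Change contrast: 2(1 - rho)
- Baseline-adjusted 6-month contrast: 1 - rho^2
- Ratio: 2(1 - rho)/(1 - rho^2) = 2/(1 + rho)
- Reduction from adjusting: 1 - (1 + rho)/2 = (1 - rho)/2, which is 35%, 25% and 15% at rho = 0.3, 0.5 and 0.7

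The reduction does not depend on the effect size.

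**4. Power under the assumptions above**, as Phi(0.35/sqrt(2 x 1.48 x factor/195) - 1.96):

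| rho | Change contrast, free baseline | Baseline-adjusted |
|---|---|---|
| 0.3 | 0.67 | 0.85 |
| 0.4 | 0.74 | 0.87 |
| 0.5 | 0.81 | 0.91 |
| 0.6 | 0.89 | 0.94 |
| 0.7 | 0.96 | 0.98 |

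**5. Sensitivity.** The rho at which the change contrast reaches 0.8 depends on inputs that the article leaves open:
- d = 0.35, ICC on change 0.24: about 0.49
- d = 0.35, ICC on change 0.15, 0.10 and 0.05: 0.42, 0.37 and 0.31
- d = 0.35, clinician effect a random intercept only, so that it cancels from change: 0.24
- ICC on change 0.24 with d = 0.40: 0.33; with d = 0.30: 0.62

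If the effect is standardized on change or on the slope, rho drops out.

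**6. The gain if the clinician effect is only a stable intercept.** The relevant correlation is then that of clinician means at two visits, r = c/(c + (1 - rho)/3), with c = 0.24 + (rho - 0.24)/3. For rho = 0.3, c = 0.26 and r = 0.26/0.493 = 0.53. For rho = 0.7, c = 0.393 and r = 0.393/0.493 = 0.80. The attainable reduction, (1 - r)/2, is then about 24% and 10% instead of 35% and 15%. A child-level covariate alone captures somewhat less than this.

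**7. Baseline imbalance.** For a chance baseline difference of 0.2 SD, the change contrast shifts by 0.2(1 - rho): 0.14 SD at rho 0.3 and 0.06 SD at rho 0.7. A baseline-adjusted contrast has no such expected shift when the imbalance is due to chance.

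**The case against.** **The defect is inferred.** The article does not say that baseline is left unadjusted. A baseline score could be among the unlisted child-level factors, and an article commonly leaves covariate lists and coding of time to the full protocol or analysis plan. This stands as a limit on the claim: the point is conditional on the natural reading. It does not remove the benefit of fixing the form.

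**Baseline as an outcome is not itself the fault.** This stands. The loss comes from leaving the baseline difference free. The same three-visit model with baseline means constrained equal has power 0.85 to 0.87 at rho 0.3 and 0.91 to 0.92 at rho 0.5, as good as covariate adjustment. The article's wording is compatible with that model.

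**A reader might infer that the power claim fails unless rho is about 0.5.** The documents do not support this. The threshold runs from about 0.24 to 0.62 over unstated inputs and disappears under the constrained model.

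**A reader might infer that the 0.24 limit came from a one-score calculation.** The match in step 1 invites this, but the fidelity figures in the same paragraph speak against it. At 195 children per condition the same formula gives 0.91 for both of them (0.35 at ICC 0.04; 0.4 at ICC 0.21), not 0.8. They give 0.8 at about 140 per condition, where the one-score client calculation gives only about 0.67. The sponsor may have used another sample size or given credit for repeated measures.

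**Selection after randomization.** Children are enrolled after clinicians are randomized. If that produces real baseline differences, covariate adjustment can itself be biased, and which method does better rests on untestable assumptions. This stands, so the imbalance argument is limited here to chance differences.

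**Conclusion.** The concern holds in a limited form. On its natural reading, the client-outcome model has the beginning-of-treatment score as one of three outcomes and names no baseline adjustment. If the baseline difference between conditions is free, the condition-by-linear-time contrast has 2/(1+rho) times the variance of an adjusted one. Adjustment then saves about 15-35% for rho 0.7 to 0.3, given the same clinician ICC for both contrasts, and less if the clinician effect is a stable intercept. The unadjusted contrast also turns chance baseline differences into apparent differences in improvement.

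It is not shown that the trial is underpowered for client outcomes, or that its power figure was computed for the wrong design. What can be said of the power line is that it lacks a numeric effect, a scale and a baseline-outcome correlation, so it cannot be tied to the contrast that will be tested. This is an improvement worth making, not a demonstrated error in the result.

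**What to change.** In the Aim 2 client-outcome model:

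- Use the 3- and 6-month scores as level-one outcomes, with time as a category.
- Enter the child's beginning-of-treatment score on the same scale as a level-two covariate.
- Keep the child and clinician levels.
- Name the condition test: at 6 months, or averaged over 3 and 6 months.
- Restate the client power line for that contrast, with the numeric effect size, its scale and the assumed baseline-outcome correlation.

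The cost is a change of model wording and one re-run calculation; no new data are needed. The downside is that a child with neither follow-up score drops out of the comparison. If the sponsor prefers to keep all three visits as outcomes, stating that baseline means are constrained equal would recover the same precision.
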